## Abstract

**Background:**

Degenerative lumbar instability (DLI) is a common disease that causes low back pain (LBP) in clinic. It is difficult to completely recover from DLI, and it occurs repeatedly, which seriously affects the quality of life of patients. The epidemiological survey showed that 20–30% of low back pain was related to lumbar instability. Increasing evidence shows that seated lumbar rotation manipulation can effectively improve the clinical symptoms of patients with low back pain. The primary aim of this clinical trial is to observe the intervention effect of seated lumbar rotation manipulation on DLI patients.

**Method/design:**

A total of 60 participants with DLI will be recruited and randomly allocated into the seated lumbar rotation manipulation group (the intervention group) or lumbar traction in supine position group (the control group) in this prospective, outcome assessor-blind, two-arm randomized controlled clinical trial. The treatment of the two groups lasted for 3 weeks, and the manipulation of the intervention group would be carried out once every other day, three times a week, a total of 9 times; the control group would be given lumbar traction once a day, five times a week, a total of 15 times. JOA (Japanese Orthopaedic Association) and VAS (Visual Analogue Scales) scores will be recorded as the primary outcomes before the treatment and at the 1st, 3rd, 5th, 8th, 10th, 12th, 15th, 17th, and 19th days after treatment and follow-up visit at the first, third, and sixth months. JOA efficacy evaluation standard will be used to evaluate the overall efficacy as the secondary outcomes.

**Discussion:**

The results of this prospective, randomized controlled trial will provide a clinical evidence for the treatment of DLI with seated lumbar rotation manipulation.

**Trial registration:**

Chinese Clinical Trial Registry ChiCTR2000032017. Registered on 18 April 2020, Prospective registration.

## Introduction

Degenerative lumbar instability (DLI) is a common disease that causes low back pain in clinic. It is difficult to completely recover from DLI, and it occurs repeatedly, which seriously affects the quality of life of patients. According to the data of the World Health Organization global disease burden research [1], among 301 diseases in 188 countries, low back pain ranks first in the disease burden indicators of developed and underdeveloped countries all the year round. In China, the disease burden caused by low back pain also ranks first. The epidemiological survey [2] shows that 20–30% of low back pain is related to lumbar instability, which shows that the disease brings huge economic and social burden.

The treatment of DLI includes non-surgical (conservative) treatment and surgical treatment. The choice of the two mainly depends on the degree of lumbar instability, the type of involved tissue, secondary deformity, the risk of complications, and psychological, social, economic and other comprehensive factors. Clinical conservative treatment of most patients with DLI can achieve good results [3, 4]. Absolutely lying in bed or strengthening the functional exercises of lumbar, back, and abdominal muscles can achieve the purpose of prevention and treatment of back pain. However, surgical treatment is limited to patients with obvious neurological symptoms, progressive aggravation of spondylolisthesis, and ineffective conservative treatment. It is generally believed that non-surgical treatment is the first choice for the treatment of DLI, such as bed rest, brace, manipulation, traction, physical therapy, and needle-knife.

The traditional Chinese manipulation has unique advantages in the treatment of lumbar and back pain, and the clinical reports [5–8] on the treatment of low back pain, lumbar disc herniation, lumbar facet joint disorder, lumbar spondylolisthesis, and other diseases with sitting rotation manipulation also show the effectiveness of this method.

Combined with the mechanism research of the manipulation [9, 10], the author believes that in the clinical treatment, first of all, the muscle can be relaxed directly through the doctor’s massage, which can achieve the purpose of loosening the adherent tissue and relieving the spasm. This can promote blood circulation and improve the ischemic and anoxic state of the lesion. At the same time, the increase of local tissue temperature can promote the repair of injured tissue and then promote the absorption of hematoma and edema caused by injury. In the application of manipulation, by rotating and pulling force, the facet joint produces prying movement, increases the intervertebral foramen, relieves the compression on the nerve root, adjusts the stress distribution of the spinal movement segment, and reconstructs the mechanical balance. In the stable position, the spine regained its stability through self-repair.

In order to evaluate the clinical effect of seated lumbar rotation manipulation in the treatment of DLI, we plan to design a prospective, randomized controlled trial. The main purpose of this experiment is to determine the influence of seated lumbar rotation manipulation on the activity limitation and clinical signs of patients with DLI.

Supine lumbar traction is one of the common treatment methods in the clinical treatment of DLI. The main function of traction is to separate the articular surface and traction the surrounding soft tissue, so as to expand the lumbar vertebral space, change the bone structure, reduce the pressure in the spinal canal, relieve the compression state of the spinal cord and peripheral nerve, and achieve the purpose of reducing the symptoms of patients. In most of the clinical studies of manipulation in the treatment of degenerative lumbar diseases, supine lumbar traction was used as the control group [11, 12].

We hypothesized that compared with the intervention of lumbar traction in supine position, seated lumbar rotation manipulation would improve the symptoms, physical signs, and activity limitation of patients.

## Method/design

### Study design

According to the random number table method [13], a total of 60 patients with DLI will be divided into sitting lumbar rotation manipulation group (the intervention group) and supine lumbar traction group (the control group), 30 cases in each group. DLI patients will be numbered according to the visit time, and any one number in the random number table will be selected as the starting point. A random number corresponding to each patient will be obtained along the same direction. Divide this number by 2, and the remainder of 0 will be the intervention group, and the remainder of 1 will be the control group. Two residents participating in this study will be responsible for generating the allocation order sequence.

The treatment of the two groups lasted for 3 weeks. The manipulation of the intervention group would be carried out once every other day, three times a week, a total of 9 times; the control group would be given lumbar traction once a day, five times a week, a total of 15 times. JOA [14] and VAS [15] scores will be recorded as the primary outcomes before the treatment and at the 1st, 3rd, 5th, 8th, 10th, 12th, 15th, 17th, and 19th days after the first treatment and follow-up visit at the 1st, 3rd, and 6th months. JOA [14] efficacy evaluation standard will be used to evaluate the overall efficacy as the secondary outcomes. When analyzing the results, the personnel who collect the data are blind to the grouping situation. The flow of this clinical trial is shown in Fig. 1; the schedule of enrolment, assessments, and interventions is presented in Table 1. JOA [14] and VAS [15] scores are presented in Table 2 and Fig. 2.

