### Randomization, allocation concealment, and blinding

Upon completion of the baseline assessment, participants were randomly assigned by the physician to the sitting lumbar rotation manipulation group and the supine lumbar traction control group. Because doctors and patients are able to know which kind of intervention will be accepted, they cannot be blind to the treatment, but the result evaluator and data statistician are blind to the grouping and treatment.

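### The odd/even allocation rule gives 30 patients per group only on average, yet the plan states 30 in each group as fixed

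*Protocol article*

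**What the plan says.** The Study design section of the protocol article opens with the size of the trial: "a total of 60 patients with DLI will be divided into sitting lumbar rotation manipulation group" or the traction group, with "30 cases in each group".

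The same paragraph then sets out the allocation method step by step:

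- Order: "DLI patients will be numbered according to the visit time".
- Draw: "A random number corresponding to each patient will be obtained along the same direction", from an arbitrary starting point in the table.
- Rule: "Divide this number by 2, and the remainder of 0 will be the intervention group", and "the remainder of 1 will be the control group".
- Responsibility: "Two residents participating in this study will be responsible for generating the allocation order sequence".

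The section on randomization, allocation concealment and blinding adds that "participants were randomly assigned by the physician to the sitting lumbar rotation manipulation group" or to traction, and that doctors and patients know the treatment while the outcome evaluator and the statistician do not. Neither section mentions a block, a cap, a redraw or any other balancing step.

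**The concern.** The paragraph gives a fixed split and a rule that does not produce a fixed split. Parity of one random number per patient is a coin toss per patient. Nothing in it steers the totals to 30 and 30, so in most realisations staff must depart from one of the two statements. Either they accept unequal groups, or they alter the sequence to reach 30 each.

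The first course is harmless apart from the wrong figure. The second could matter. Once one arm is full, every later patient goes to the other arm, and anyone who can count past allocations knows this in advance. Treatment is open to doctors, and the physician makes the assignment, so the decision to enrol a late patient could be influenced by the known arm. VAS, a primary outcome marked by an unblinded patient, would be sensitive to such selection.

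**Working it through.** **Inputs.** From Study design: N = 60, stated sizes 30 and 30, one random number per patient, even to intervention and odd to control. Assumptions: the table's numbers are independent, even and odd are equally likely, and exactly 60 patients are randomised.

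**1. The plan's figure under its own rule.** The intervention count X is Binomial(60, 0.5).

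- Expected size: 60 × 0.5 = 30. The stated figure is reproduced as a mean.
- P(X = 30) = C(60,30)/2^60 = 0.1026. The stated split is missed with probability 1 − 0.1026 = 0.897.
- P(28 to 32 in one arm) = 0.481.
- P(33:27 or worse) = 0.519.
- P(35:25 or worse) = 0.245.
- P(38:22 or worse) = 0.052, so 23 to 37 in one arm covers 94.8%.

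**2. Cost of imbalance alone.** With equal variances, efficiency relative to 30:30 is 4·n1·n2/N².

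- 35:25 gives 4 × 35 × 25 / 3600 = 0.972, a loss of 2.8%.
- 38:22 gives 4 × 38 × 22 / 3600 = 0.929, equivalent to about 55.7 balanced patients.

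**3. If exactly 30:30 were enforced** (a scenario, not something the article describes). Let T be the number of final allocations that are certain because the other arm is full. T is at least 1 under any fixed 30:30 total.

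- *Arm closed when it reaches 30.* P(T = t) = 2·C(59−t, 29)/2^(60−t), for t = 1 to 30. These sum to 1. Mean T = 6.15, P(T ≥ 5) = 0.590, P(T ≥ 10) = 0.203. The mean is about 10% of the sample (6.15/60).
- *Random ordering of 30 and 30 prepared in advance.* The mean final run of one arm is 2 × 30/31 = 1.94, about 3% of the sample (1.94/60).

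**4. Same measure for the usual remedy.** Take, as an example, six blocks of 4 and six blocks of 6: 6 × 4 + 6 × 6 = 60, which gives 30:30 by construction. If block sizes became known, the determined allocations would average 6 × 4/3 + 6 × 1.5 = 17. Blocks therefore need undisclosed, randomly varying sizes and real concealment.

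**The case against.** The strongest reply is that 30 per group is simply the 1:1 target. The split appears once. The abstract and the Sample size section commit only to 60, and 60 was chosen without a calculation, so nothing statistical rests on exactly 30 each. Simple randomisation is valid and is the least predictable scheme available. A journal article also condenses, so a balancing step and the concealment procedure may stand in the full protocol, and the source cited for the random number table method cannot be consulted here.

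Much of this stands. The missing concealment detail is not held against the plan, and unequal arms would not bias the comparison. What does not stand is that condensing explains the mismatch: the article gives the allocation rule in full, down to the remainder on division by 2, beside a fixed split that the rule does not guarantee. Nor does the text present 30 as a target or an expectation.

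A reader might go further and infer that the rule cannot yield 30:30, or that late allocations in this trial are predictable. The documents support neither. An even split arises by chance about one time in ten. No cap, override or filling of the smaller arm is described, and nothing says that those who select patients keep a count or see the sequence.

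**Conclusion.** The point holds as an inconsistency between the stated method and the stated group sizes. Under independent draws with equal chances for 60 patients, the split of 30:30 occurs with probability 10.3%, and a split of 35:25 or worse with probability 24.5%. The direct statistical cost is small.

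The more serious consequence is conditional on enforcement of exactly 30:30. It then ranges from about 1.9 to about 6.2 determined allocations out of 60, depending on how balance is reached, and it affects only the end of recruitment. The larger figure applies only to closing an arm at 30; it is not a general result. The contradiction is worth correcting because it leaves staff without a clear instruction when the arms drift apart, in a setting where treating doctors are unblinded and the physician assigns. It is not evidence that allocation in this trial was compromised.

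**What to change.** Make the method and the sizes agree, in one of two ways.

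1. *If 30 per group is required:* replace the parity rule with a restricted 1:1 list generated in advance, for example permuted blocks of randomly varying, undisclosed size totalling 60. It should be prepared by someone who neither enrols nor treats, and concealed from those who recruit and assign. Generating the list takes minutes. The price is some predictability if block sizes become known, which is why concealment must be stated along with the list.
2. *If the parity rule is kept:* change the size statement to 'about 30 per group', and state that the sequence will not be overridden to equalise the arms. This is a wording change only. It accepts unequal groups at the small efficiency cost shown above.

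Either option resolves the point. If patients have already been allocated, the report should state the method actually used, whether any balancing step was applied, and the group sizes obtained.

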### Outcome assessment

Variables for this clinical trial included the patient’s baseline, primary, and secondary outcomes.

The baseline will be completed before treatment, and the primary and secondary results will be measured at baseline and on the 1st, 3rd, 5th, 8th, 10th, 12th, 15th, 17th, and 19th days after the first treatment, and followed up at the 1st, 3rd, and 6th months. All primary and secondary outcomes will be evaluated by experienced doctors at Wangjing Hospital, and patient allocation results will be blind to them.

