#### Primary outcomes

We will use the Japanese Department of orthopedics Association (JOA [14]) low back pain rating scale (Table 1) to observe and record the symptom and sign scores of the two groups of patients at each visit point. The parameters in the scoring table are divided into four parts. The maximum score is 29 points, and the minimum score is −6 points. The higher the score the more normal the patient’s overall status. VAS [15] will be used to observe and record the pain degree of each visiting point in the two groups (Fig. 2), which means marking the numbers 0–10 with a straight line divided into 10 equal parts, according to the patient’s degree of pain to determine and draw on the corresponding number, and finally by the doctor according to the patient’s mark on the scale of the number to score. If the patient is marked on 5, it will be recorded as 5 points.

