### Statistical analysis

An independent statistician will use the SPSS V.25.0 software to perform the statistical analysis. Count data and grade data will be described by the number of case. The counting data will be tested by χ^2^; Wilcoxon rank-sum test will be applied to rank data. The measurement data will be statistically described with mean ± standard deviation. In group comparison, paired sample t-test will be applied. The rank sum test will be used for the difference comparison between groups. *P* < 0.05 will be considered statistically significant.

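### JOA and VAS are both primary at all 12 post-baseline visits with no primary visit, ranking or success rule, so the false-positive risk is several times the nominal 5%

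*Protocol article*

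**What the plan says.** Study design in the protocol article sets the primary outcomes and their timing in one sentence: "JOA [14] and VAS [15] scores will be recorded as the primary outcomes before the treatment and at the 1st, 3rd, 5th, 8th", continuing with "10th, 12th, 15th, 17th, and 19th days after the first treatment and follow-up visit at the 1st, 3rd, and 6th months". The Abstract gives the same list. Outcome assessment repeats it for all outcomes: "the primary and secondary results will be measured at baseline and on the 1st, 3rd, 5th, 8th, 10th, 12th" and onward. Under Primary outcomes, JOA is used to "observe and record the symptom and sign scores of the two groups of patients at each visit point", and VAS is likewise recorded at every visit.

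For comparing the arms on scores, Statistical analysis says: "The rank sum test will be used for the difference comparison between groups". The only decision rule is that P "< 0.05 will be considered statistically significant". The article names no primary visit, no summary over time, no order between JOA and VAS, and no rule on whether one or both must succeed.

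Three other statements bear on the point. Sample size calls the study exploratory and gives no calculation for the 60 patients. The Introduction states a superiority hypothesis against traction and gives the main purpose as to "determine the influence of seated lumbar rotation manipulation on the activity limitation and clinical signs of patients with DLI". The Discussion part of the Abstract expects the results to provide clinical evidence for the treatment.

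**The concern.** A primary outcome is meant to fix, before the data are seen, which single result decides the question. Here the label covers every visit on two scales. A difference in VAS at day 3 and a difference in JOA at month 6 answer different clinical questions, yet either could be reported as the primary result. With no rule for choosing among them, the 5% threshold does not describe the trial's chance of a false-positive primary finding. A reader of the final report could not tell whether the headline visit was planned or picked.

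**Working it through.** **1. Inputs.** From Study design and Outcome assessment: 2 primary outcomes; 9 visits on days 1, 3, 5, 8, 10, 12, 15, 17 and 19; 3 follow-up visits at months 1, 3 and 6; 30 patients per arm. From Statistical analysis: rank sum test between groups and threshold 0.05, with sidedness not stated (two-sided assumed). The article gives no correlations, so those below are assumptions. It also gives no family-wise error rate and no power, so there is no planned figure to reproduce.

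**2. Count.** 9 + 3 = 12 visits; 2 × 12 = 24 candidate primary comparisons.

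**3. Independence, as an upper reference only.** Chance of at least one P < 0.05 with no effect = 1 − 0.95^k.
- k = 2 (both outcomes, one visit): 1 − 0.95² = 9.75%
- k = 12 (one outcome, all visits): 1 − 0.95¹² = 46%
- k = 24: 1 − 0.95²⁴ = 70.8%

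**4. Correlated tests.** The 24 test statistics were drawn as multivariate normal with mean zero, and a run counted if any |z| > 1.96 (400,000 draws per setting). The correlation matrix is the 2 × 2 JOA–VAS matrix crossed with a 12 × 12 between-visit matrix. Both scales are oriented so that higher is better. With equal correlation r between all visits:

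| r between visits | JOA–VAS 0.3 | JOA–VAS 0.5 | JOA–VAS 0.7 |
|---|---|---|---|
| 0.5 | 52.7% | 50.8% | 47.7% |
| 0.7 | 40.2% | 38.5% | 35.5% |
| 0.9 | 24.5% | 23.3% | 21.5% |

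- For r = 0.5–0.9 and JOA–VAS correlation 0.4–0.6 the range is about 22–52%. Against 5%, that is 22/5 = 4.4 to 52/5 = 10.4 times nominal.
- Counting only results that favour manipulation (nominal 2.5%), the range is 11–27%. At JOA–VAS correlation 0.4 it is 27%, 20% and 12% for r = 0.5, 0.7 and 0.9.
- With correlation that decays over successive visits (AR(1), 0.8–0.95), the two-sided range is 26–48%.
- Over the widest settings tried (between-visit 0.3–0.95, JOA–VAS 0.3–0.7, both structures), it is 17–68%.

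**5. Check with the planned test.** Simulated rank sum tests at 30 versus 30 (6,000 runs per setting) agree: 53% (r = 0.5, JOA–VAS 0.5), 41% (0.7, 0.5), 22% (0.9, 0.7), and 50% (AR(1) 0.8, JOA–VAS 0.5).

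**6. After a repair.** One outcome at one visit: 5%. JOA then VAS at the same visit in fixed sequence: at most 5%. Both at one visit, each at 0.025: at most 5%. Both at one visit, each at 0.05 with either sufficing: about 8–10%.

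Keeping all 24 under Bonferroni needs 0.05/24 = 0.0021 each. The difference detectable with 80% power is (z for α + 0.842) × √(2/30), by normal approximation:
- α = 0.05: (1.960 + 0.842) × 0.258 = 0.72 SD
- α = 0.025: (2.241 + 0.842) × 0.258 = 0.80 SD
- α = 0.0021: (3.078 + 0.842) × 0.258 = 1.01 SD

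So adjusting for all 24 would cost a trial of this size far more than choosing one visit.

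**The case against.** The strongest defence has three parts.

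First, the article says scores are recorded at every visit. It does not say that a test is run at every visit. This is right, and the 24 comparisons are an inference. They remain the natural reading, because for scores only paired t-tests and a rank sum test are named and no model combines the visits.

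Second, a statistical analysis plan may exist, and the article condenses a fuller protocol. Multiplicity adjustment, testing order or a longitudinal model could sit there, so the absence of adjustment from the article is not itself a finding. That part of the defence stands. It does not cover the choice of primary endpoint and visit, which is a core protocol element. The article is not silent on it: it attaches the primary label to every visit of both scales.

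Third, the study is declared exploratory, and strict family-wise error control belongs mainly to confirmatory claims. This lowers the gravity but does not settle the matter. The remark appears as the reason for having no sample size calculation and puts no limit on the claims. The primary label, the superiority hypothesis, the significance threshold and the expected clinical evidence all remain.

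A reader might infer that a false-positive primary result is more likely than not, citing 71%. That figure needs 24 independent tests, which two scales measured repeatedly in the same 60 patients cannot supply. Under the main assumed correlations the chance is mostly below one half.

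**Conclusion.** The point holds in this form: the article leaves up to 24 candidate primary results and no rule for choosing among them. With no true difference, the chance of at least one P < 0.05 is about 22–52%, or 11–27% in favour of manipulation, which is several times nominal. This rests on three things: testing at each visit (inferred), two-sided tests at 0.05, and the assumed correlations with equal correlation between visits. Other structures and wider assumptions move the figure, but the lowest value found, 17%, is still more than three times 5%.

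The documents do not support calling a false positive likely, or describing 24 tests as the stated plan. Given the declared exploratory status, this is something that should be fixed, not a defect that invalidates the trial.

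**What to change.** Amend the Abstract, Study design, Primary outcomes and Statistical analysis before anyone looks at outcome data by arm.

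- Name one primary endpoint at one visit. A suitable choice is JOA total at day 19 after first treatment, the last listed visit in the three-week treatment period. JOA fits the stated main purpose: its clinical signs and activity sections carry 6 + 14 = 20 of the 29 points.
- Test VAS at the same visit second, only if JOA is significant. Ranking JOA first is a judgement, since the hypothesis also names symptoms. Splitting alpha at 0.025 each, or requiring both to succeed, would also serve.
- Keep the visit schedule. Report all other visits and the JOA improvement rate as estimates with 95% confidence intervals and no significance claims.
- If the study is to stay wholly exploratory, remove the significance claim from every comparison instead.

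The change needs no extra patients or data. The price is that fewer results can be called significant. There is also a selection risk: Trial status puts the start of recruitment at 1 May 2020, and doctors and patients know the allocation, although the evaluator and statistician do not. The amendment must therefore be dated and state that the visit was chosen without sight of outcome data by arm. The registry record was not available here; it should be checked for consistency with the amended text.
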